#### Statistical analyses

Analyses of covariance and regression methods will compare primary and secondary outcomes between intervention and control groups at 24 months, adjusting for baseline outcome values and any imbalance in other covariates as appropriate.

Analyses will be by intention-to-treat. It will be necessary to consider any difference in attrition rates, and the non-randomness of the attrition, when comparing quality of life between the two groups. In the pilot RCT only 7/126 (5.5 %) died during the 24 month follow-up, so it is thought unlikely that methods for joint modelling of survival and longitudinal data will be necessary.

Exploratory sub-group analyses will also be undertaken, for example to examine differences in outcome between men and women, by age and by amount and type of benefits received.

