### Pragmatic versus explanatory

Not all participants in the intervention group will be eligible for additional benefits, and for those who are, they may receive variable amounts of financial and non-financial benefits. Ideally, we would wish to examine the health impact of receiving versus not receiving such benefits, as well as examining the potential for a gradient of effect (‘dose-response’ relationship) by amount of benefit received. However, to do so would require a substantially larger sample size. In practice, therefore, the receipt of welfare rights advice is the intervention we are evaluating (rather than receipt of specific benefits), since ‘welfare rights advice’ is the service being delivered. The proposed trial is therefore a pragmatic (intention-to-treat) RCT of this complex intervention. Nevertheless, we will also assess the potential for exploratory sub-group analyses looking at differential effects by participant characteristics (such as age and sex), receipt/non-receipt of, and levels of any benefits received. We anticipate that the trial will therefore contribute both to answering the question of whether the complex welfare rights advice intervention is effective in improving health and to providing new evidence on the theoretical question of whether increasing resources leads to better health [9].

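### Sub-group analyses by benefits received condition on a result of allocation, so they can mislead on whether resources improve health

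*Protocol article*

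**What the plan says.** The Statistical analyses section states that "Exploratory sub-group analyses will also be undertaken" and gives as examples "differences in outcome between men and women, by age and by amount and type of benefits received". In the Discussion, Pragmatic versus explanatory describes exploratory analyses "looking at differential effects by participant characteristics (such as age and sex), receipt/non-receipt of, and levels of any benefits received". It then expects the trial to contribute to "providing new evidence on the theoretical question of whether increasing resources leads to better health".

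The same section says that the authors would ideally study receipt against non-receipt and a dose-response gradient. The one limitation it gives is "However, to do so would require a substantially larger sample size". It does not mention that these comparisons lose the protection of randomisation.

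Three other sections matter here:
- Secondary outcome measures: new benefits since baseline are recorded at follow-up.
- Comparator (wait-list control condition): controls receive no study advice until after their 24-month assessment.
- Statistical analyses: the main comparison is by intention-to-treat.

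**The concern.** The list mixes two kinds of variable. Sex and age are fixed before randomisation, so arms can be compared within their levels. Benefits received is what the intervention is meant to change, and most of the difference between arms in new benefits will come from allocation.

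Receipt is also unlikely to be unrelated to prognosis. The Background says that unclaimed entitlements are disproportionately health-related, and that older people in poor health need more income and support. Recipients are therefore probably sicker or more needy than non-recipients, and recipients in the two arms are differently selected.

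At stake is the trial's secondary claim about resources and health. A contrast by receipt, type or amount could suggest that extra income harms or helps when it does neither, or could mask a true gain. More participants would estimate the bias more precisely and would not remove it.

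**Working it through.** **Inputs from the Protocol article.** SD 8.7, baseline to 24-month correlation 0.74, target 1.5 units, 90% power, 5% significance, 15% attrition (Trial sample size and power); 58% gaining benefits in the pilot (Welfare rights advice services and their evaluation), taken here as the share in the intervention arm.

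**Assumptions, not in the article.** 10% of controls gain benefits. Receipt is decided by a normally distributed need score crossing a threshold. Need correlates 0.1 to 0.3 in size with a lower baseline-adjusted 24-month score. The true effect is zero.

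**Step 1: the plan's own figure.** Residual SD = 8.7 × √(1 − 0.74²) = 5.85. For 1.5 units, two-sided 5% and 90% power, n = 320 per arm, 640 in total; 640/0.85 = 753. This agrees with the stated 750, which gives 89.9% power. The same residual SD is used below.

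**Step 2: mean need by group.** If a share p receives benefits, mean need is φ(z)/p in recipients and −φ(z)/(1 − p) in non-recipients, where z is the threshold.
- Intervention, p = 0.58: φ = 0.391, so 0.674 and −0.931.
- Control, p = 0.10: φ = 0.1755, so 1.755 and −0.195.

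**Step 3: spurious differences.** Each equals −(difference in mean need) × correlation × 5.85.

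| Contrast, zero true effect | Difference in need | Correlation 0.1 | Correlation 0.3 |
|---|---|---|---|
| Recipients minus non-recipients, intervention arm | +1.605 | −0.94 | −2.82 |
| Recipients, intervention minus control | −1.081 | +0.63 | +1.90 |
| Non-recipients, intervention minus control | −0.736 | +0.43 | +1.29 |

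The first row does not use the assumed 10%. Within the intervention arm benefits look harmful; across arms, in both strata, the intervention looks helpful. All of this arises with no effect.

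**Step 4: a second model as a check.** Suppose that would-be recipients (58% of each arm) score d units lower after baseline adjustment and that no control receives benefits. For scale, d is set to 1.1, 1.8 and 2.8, values among the CASP-19 examples in Trial sample size and power. Those examples describe changes in circumstances, not recipients against non-recipients. Simulation used 319 completers per arm and ANCOVA on baseline.

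| Contrast, zero true effect | d = 1.1 | d = 1.8 | d = 2.8 |
|---|---|---|---|
| Intervention recipients v all controls | −0.48 (14% false positive) | −0.76 (29%) | −1.17 (56%) |
| Intervention non-recipients v all controls | +0.63 (18%) | +1.03 (40%) | +1.62 (74%) |
| Recipients v non-recipients, intervention arm | −1.10 (38%) | −1.80 (76%) | −2.78 (98%) |

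The intention-to-treat comparison stayed at about zero with about 5% rejection. With d = 0, every contrast was unbiased.

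**Step 5: a real effect hidden.** If only recipients gain and the overall effect is 1.5, each recipient gains 1.5/0.58 = 2.59. Recipients minus non-recipients in the intervention arm then showed +1.5, +0.8 and −0.2 for the three values of d.

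**The case against.** The strongest reply is that the article specifies very little. It calls the analyses exploratory, gives them as examples, and in the Discussion says only that their potential will be assessed. It names no contrast, and the method may be set out in a fuller document. The evaluated intervention is explicitly the advice, not the benefits, and the sentence about resources and health has the whole trial as its subject.

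Part of this stands. A reader might infer that the plan commits to comparing recipients with all controls, or that it rests a formal causal claim on the sub-groups; the text does neither. The link to the resources question is a single therefore that follows the sub-group sentence. But the point does not depend on which contrast is chosen, because any stratification on observed benefits loses the randomised comparison. The exploratory label limits the strength of the claim without touching bias.

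It also stands that the article does not quantify the prognostic gap. The 10% for controls is likewise assumed: the only evidence given is that no pilot control sought advice over six months.

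Finally, an instrumental-variable analysis is no clean substitute. Advisors also help with other welfare issues (Intervention), so advice may act without any new benefit, which puts the exclusion restriction in doubt.

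**Conclusion.** The point holds as one about secondary, exploratory inference. Analyses by receipt, amount or type of benefits can give spurious effects or hide real ones. Under the stated assumptions the error runs from about 0.4 to 2.8 CASP-19 units, against a target of 1.5. Direction and size depend on how far recipients differ in prognosis after baseline adjustment; the article makes a difference likely but gives no figure, and with no difference there is no bias.

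Two stronger readings are not supported. A reader might infer that the main result is compromised; it is not, since the primary analysis is by intention-to-treat, and the sex and age sub-groups are sound. A reader might also infer that spurious effects are certain; the documents support only that they can occur.

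**What to change.** - Keep sex and age as sub-group variables.
- Replace benefits received as an effect modifier with an arm-by-covariate interaction on entitlement predicted from baseline income, benefits, capital and function, which are collected in both arms before randomisation. Derive the score only at analysis, after the 24-month assessments, because Equipoise and the control condition regards identifying controls' eligibility while withholding it as ethically problematic.
- If an effect of resources is wanted, add a complier-average (instrumental-variable) estimate as a secondary sensitivity analysis. State that the exclusion restriction is doubtful. Treat receipt and pounds per week gained as alternative models, since one randomised arm cannot separate them. For scale, an intention-to-treat effect of 1.5 corresponds to 1.5/0.58 = 2.6 units per complier with no control receipt, or 1.5/(0.58 − 0.10) = 3.1 with 10%.
- Label any tabulation by benefits received as a non-randomised association.
- Amend Pragmatic versus explanatory so that the resources-and-health inference does not rest on such tabulations.

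The cost is wording, analyst time, a wide interval for the complier estimate and an assumption that must be stated. No new data are needed.

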#### Health economic analyses

The economic evaluation will consist of a cost analysis conducted from the perspectives of public sector services (‘Do-Well’ service delivery costs), and that of the Treasury (total cost of additional benefits paid out). The mean change in benefits and the mean change in total income of participants will also be calculated.

The cost analyses above will be used in conjunction with study outcomes to produce a cost consequences analysis [49]. If any significant change in EQ-5D health utility scores can be attributed to the intervention, we will undertake a cost-utility analysis [49]. The assumptions that underpin any such cost-utility analysis will be subjected to one-way sensitivity analysis [50] and, in addition, extensive probabilistic sensitivity analysis [50] will be used with results presented in the form of cost-effectiveness acceptability curves [50].

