## Objectives

The proposed RCT with embedded economic and qualitative process evaluations aims to answer the following questions:

1. What are the effects on health-related quality of life of a domiciliary welfare rights advice service targeting independent-living, socio-economically disadvantaged older people (aged ≥60 yrs) identified via primary care?

2. What are the cost consequences and what is the cost-effectiveness of a domiciliary welfare rights advice service targeting independent-living older people (aged ≥60 yrs) identified via primary care?

3. What is the acceptability to trial participants and relevant professionals of a domiciliary welfare rights advice service targeting independent-living older people (aged ≥60 yrs) identified via primary care?

4. What are the unanticipated consequences (positive or negative) of a domiciliary welfare rights advice service targeting independent-living older people (aged ≥60 yrs) identified via primary care?

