### Secondary outcome measures

The following secondary outcomes, based on the findings of previous research, including our own systematic review, qualitative study and pilot trial [7,8,20-22,32,37] will be collected:

· *Health status*, measured by the EuroQoL (EQ5D) [38]

· *Functional ability* measured by the modified Townsend activities of daily living scale [39]

· *Independence* categorised as: living independently or with carer support, in own home, with relations, care home or hospital (the latter two categories at follow-up only)

· *Mental health* measured by the PHQ-9 depression questionnaire [40-42]

· *Health-related behaviours* assessed by self-report to measure change in key indicator behaviours, such as smoking, alcohol consumption, diet (consumption of key food groups) and physical activity, as in our pilot RCT [7]

· *Mortality* assessed by identifying deaths at 12 months and 24 months from GP records (we will do this prior to commencing follow-up assessments, so as not to attempt to contact the recently deceased, which may cause distress to bereaved relations)

· *Social support and participation* measured by the Social Support Questionnaire [43].

· *Perceived financial wellbeing* measured by the Affordability Index [44].

· *Fuel poverty* measured where a household can achieve temperatures needed to maintain health and comfort for expenditure of less than 10 % of income [45]

· *Financial status* measured by a standard assessment tool developed and used in our pilot RCT [7]. This includes data on all sources of household income, including benefits, major outgoings (rent/mortgage, fuel bills etc.), debts and capital assets (i.e. home and savings). As well as these data, at follow-up detailed data will be collected (by WR Advisors) on new benefits received since baseline, including one-off (lump sum) payments and regular, weekly or monthly income.

· *Material (dis)advantage* measured through standard questions to ascertain home ownership, size of home (number of ‘living’ rooms), car ownership, and access to household amenities (such as central heating, cooker, fridge, freezer, etc.).

These outcomes will be assessed by structured, face-to-face interview at baseline (pre-randomisation) and 24 months post-randomisation.

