### Sample size

#### Trial sample size and power

A minimum of 750 participants will be randomised to intervention and control arms, providing 90 % power at 5 % significance level to detect a 1.5 unit difference in mean CASP19 score [35,36] between intervention and control groups, assuming a standard deviation of 8.7 and a correlation between baseline and 24 months of 0.74 [48], and 15 % attrition over 24 months (as experienced in our pilot RCT) [7]. There has been no published work to establish a meaningful or clinically important difference on the CASP19 scale. However, we have used data from two waves of the English Longitudinal Study of Ageing in those aged ≥60 yrs to investigate the adjusted mean difference in CASP19 at Wave 2 between groups whose social or health circumstances had changed [48].

Examples of changes in CASP19 score associated with changes in health or social circumstances that we might expect to see in the proposed trial include: ‘developed limiting illness’ -2.8 units; ‘developed depression’ -2.7units; ‘lost access to car’ -1.8 units; ‘increased chance will not meet financial needs’ -1.1 units. These differences on the CASP19 scale suggest that a difference of 1.5 units would represent a ‘clinically’ important difference.

The chosen sample size should also provide power to demonstrate some clinically significant differences in secondary outcomes. For example, 750 participants will provide 90 % power to detect a difference between a prevalence of 11 % and 4 % of clinically significant depressive symptoms (PHQ-9 score ≥10).

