### Randomisation

Following baseline measurements, participants will be randomised in a 1:1 ratio to intervention or control condition. Research interviewers will notify the project administrator after each baseline interview that a new participant has been successfully recruited. The administrator will hold sequential allocation tables for each practice, independently generated from random numbers prior to recruitment. The administrator will allocate all participants to intervention or control group in the sequence that they are recruited and immediately send each participant a standard letter informing them of their group allocation. The administrator will also immediately inform the appropriate WR Advisor of the contact details of each newly allocated intervention group participant and indicate that they are to be seen within 2 weeks. WR Advisors will be sent lists of control group participants to assess 24 months later. The research interviewers will not be notified of allocation status to ensure that they remain blinded for the duration of the study.

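### Objective 2 asks for cost-effectiveness outright, but the cost-utility analysis runs only after a significant EQ-5D change, so that half of the objective may go unanswered

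*Protocol article*

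**What the plan says.** Objective 2 of the protocol article has two parts: "What are the cost consequences and what is the cost-effectiveness of a domiciliary welfare rights advice service". Neither part carries a condition.

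The Health economic analyses section treats the two parts differently.

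- **Cost consequences.** This part is unconditional: "The cost analyses above will be used in conjunction with study outcomes to produce a cost consequences analysis".
- **Cost-effectiveness.** The only analysis offered is conditional: "If any significant change in EQ-5D health utility scores can be attributed to the intervention, we will undertake a cost-utility analysis". The one-way sensitivity analysis, the "extensive probabilistic sensitivity analysis" and the acceptability curves are all attached to that cost-utility analysis, so they are done only if it is done. No alternative, such as cost per CASP-19 unit, is described.

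EQ-5D is listed under Secondary outcome measures. The Trial sample size and power section sizes the trial on CASP-19 and gives no EQ-5D effect, standard deviation, correlation or power.

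**The concern.** A cost-effectiveness estimate combines an incremental cost and an incremental effect, each with uncertainty. Probabilistic sensitivity analysis and acceptability curves show a decision-maker that joint uncertainty, and they are most useful when the effect is imprecise. The plan names these tools and then withholds them when the EQ-5D result is not significant. A non-significant difference is not evidence that the QALY gain is zero.

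Two things are at stake. If the condition is not met, the trial produces no answer to the cost-effectiveness half of a numbered objective. If it is met by a significant benefit, the gain entering the ratio has been selected for being large. On average it then overstates the truth and makes the service look better value than it is.

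**Working it through.** **Inputs from the protocol article.** Trial sample size and power: "A minimum of 750 participants will be randomised to intervention and control arms", with 15% attrition, a CASP-19 difference of 1.5, SD 8.7, baseline to 24-month correlation 0.74, 90% power and 5% significance (two-sided assumed). Randomisation: "participants will be randomised in a 1:1 ratio to intervention or control condition". Statistical analyses: comparison at 24 months adjusted for baseline.

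**Step 1: reproduce the stated sample size.** The residual SD after baseline adjustment is 8.7 × √(1 − 0.74²) = 5.85. Then n per arm = 2 × (1.960 + 1.282)² × 5.85² / 1.5² = 320, or 640 in total. Allowing for attrition, 640 / 0.85 = 753, against the stated 750. With 750 × 0.85 / 2 = 318.75 analysed per arm, power is 89.9%. The plan's figure reproduces, so 318.75 per arm is a fair basis for EQ-5D too.

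**Step 2: precision for EQ-5D.** Work in SD units, because no EQ-5D standard deviation is given. The baseline correlation r is also not given. It is assumed to lie between 0.5 and 0.74, the upper end being borrowed from CASP-19.

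SE = √(2 / 318.75) × √(1 − r²)

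- r = 0.5: 0.0792 × 0.866 = 0.0686, so the smallest significant difference is 1.96 × 0.0686 = 0.134 SD
- r = 0.74: 0.0792 × 0.673 = 0.0533, so the smallest significant difference is 0.104 SD

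**Step 3: chance that the cost-utility analysis is run, and inflation when it is.** For a true effect d, let t = d / SE. The chance of a significant benefit is P = Φ(t − 1.96), and the lower tail adds little. Given a significant benefit, the mean estimate divided by the truth is 1 + φ(1.96 − t) / (t × P).

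Example with d = 0.10 SD and r = 0.5: t = 0.10 / 0.0686 = 1.46, P = Φ(−0.50) = 0.31, and inflation = 1 + 0.352 / (1.458 × 0.308) = 1.78.

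| True EQ-5D effect | Analysis run (r = 0.5 to 0.74) | Mean estimate ÷ truth, given significant benefit (r = 0.74 to 0.5) |
|---|---|---|
| 0 | 5% | not defined |
| 0.05 SD | 11-16% | 2.6-3.4 |
| 0.10 SD | 31-47% | 1.45-1.78 |
| 0.15 SD | 59-80% | 1.12-1.30 |
| 0.172 SD (1.5 / 8.7) | 71-90% | 1.06-1.19 |
| 0.20 SD | 83-96% | 1.02-1.10 |

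With the condition removed, the analysis is reported in every trial and there is no selection on significance.

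**The case against.** The strongest reply is that little is lost. The two-perspective cost analysis, the change in benefits and income, and the cost consequences analysis are always done. EQ-5D is one of the outcomes that can be set beside those costs. The EQ-5D comparison is itself an intention-to-treat secondary analysis, reported whatever its p-value. All of this stands: only the derived cost-utility result is conditional. It narrows the point to the cost-effectiveness half of Objective 2 but does not remove it, because that half has no other analysis.

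The article states no test or threshold for a significant change, and elsewhere it uses the word in a clinical sense. Statistical significance is the likelier meaning, but it is an assumption here. A condition based on clinical importance would equally leave the cost-effectiveness question open when it is not met. As worded, the condition could also be met by a significant harm.

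A reader might go further and infer that Objective 2 will be unanswered in most plausible outcomes. The documents do not support this. They give no EQ-5D effect, SD or correlation, and at the standardised CASP-19 design effect the analysis would usually run, with modest inflation.

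A reader might also infer that, because "These outcomes will be assessed by structured, face-to-face interview at baseline (pre-randomisation) and 24 months post-randomisation", QALYs must be interpolated in a straight line, against the article's own view that substantial health impact within 12 months is unlikely. The article states no interpolation method. It leaves room for sensitivity analysis of the assumptions, and a condensed article may leave such detail to the full plan. That is not a fault that can be shown here.

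**Conclusion.** The point holds in a limited form. The stated rule conflicts with an unconditional objective and can leave its cost-effectiveness half without an answer. This is an explicit decision rule in the text, not a detail lost to condensation.

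The size depends on the true EQ-5D effect, which is unknown. At about 0.10 SD or below, the analysis would be run in fewer than half of trials, and a selected gain would overstate the truth by 45% or more on average. At 0.172 SD it would be run in most trials, and the overstatement is 6-19%. These figures rest on two-sided 5% significance, 15% attrition, a normal approximation and an assumed correlation of 0.5 to 0.74.

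The primary outcome, the sample size and the main effectiveness analysis are unaffected. This is something that should be fixed; it does not threaten the trial.

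**What to change.** Delete the condition. State that the cost-utility analysis will be done whatever the EQ-5D result, reporting incremental costs, incremental QALYs and their joint uncertainty through the probabilistic sensitivity analysis and acceptability curves already planned. If the EQ-5D difference is small or imprecise, the curves will show that.

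The cost is one sentence in the economic plan and a little more analysis work. It needs no additional participants or data beyond what the conditional analysis would already require.
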